#### Quality-adjusted life years

Health-related QOL will be assessed using the EQ-5D-5L at baseline and post-intervention, with utility values derived from country-specific tariffs. The area under the curve method will estimate QALYs over the intervention period, reflecting the intervention’s impact on participants’ quality and quantity of life.

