### Outcome measures

All study participants will attend two sessions at the clinical site: at baseline (week 0) and post-intervention (week 10), where a blinded outcome assessor will collect outcome measure data. Participants will be asked to complete a subjective questionnaire set, walking/balance tests, a verticality perception test and a cognitive screen. These will take approximately 1.5 hours, including comfort breaks. Participants’ e-health literacy will only be collected at baseline, while system usability score (SUS) and User Experience Questionnaire (UEQ) will be collected post-intervention among the IG only.

The outcome assessor will be asked to record any incidences of unblinding and detail how this occurred. Due to the nature of this study, we do not foresee circumstances where emergency unblinding of the outcome assessor is required.

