#### Secondary outcome measures

Various secondary outcome measures will be used to assess clinical outcomes, programme effectiveness, system performance, AI model predictive power, e-health literacy and user experience. Please see table 2 for the detailed schedule of assessments.

**Table 2 T2:** Schedule of assessments for all participants enrolled in the TeleRehaB DSS study

		Screening	Baseline	Week 0	Weekly	Weeks 3 and 6	Post-intervention (week 10)	Monthly
Recruitment procedures	PIS informed consent	X	X					
Data collection and outcome measures	Demographics		X					
	HADS	X					X	
	DHI	X					X	
	FGA	X					X	
	MoCA	X					X	
	EQ-5D-5L		X				X	
	RAPA		X				X	
	ABC		X				X	
	Mini-BESTest		X				X	
	SVV		X				X	
	WEMWBS		X				X	
	FSS		X				X	
	SVQ		X				X	
	Exit interviews						X	
User experience measures	SUS						X	
	UEQ						X	
eHealth literacy measures	eHEALS		X					
	STAM-14		X					
	MDPQ-s		X					
Home-based interactions	Equipment installation and practice session (*IG only*)			X				
	Equipment de-installation (*IG only*)						X	
	Telephone call				X			
	Remote programme review					X		
	Perform HEP				X			
	Submit falls diary				X			X
	Submit exercise log				X			

ABC, Activities Specific Balance Confidence Scale; DHI, Dizziness Handicap Inventory; eHEALS, eHealth Literacy Assessment; EQ-5D-5L, EuroQol five-dimensional descriptive system; FGA, Functional Gait Assessment; FSS, Fatigue Severity Scale; HADS, Hospital Anxiety and Depression Scale; HEP, home exercise programme; IG, intervention group; MDPQ-s, Mobile Device Proficiency Questionnaire - short; Mini-BESTest, Mini-Balance Evaluation Systems Test; MoCA, Montreal Cognitive Assessment; PIS, Participant Information Sheet; RAPA, Rapid Assessment of Physical Activity; STAM, Senior Technology Acceptance and Adoption Model-14; SUS, System Usability Scale; SVQ, Situational Vertigo Questionnaire; SVV, Subjective Visual Verticality; TeleRehaB DSS, TeleRehabilitation Decision Support System; UEQ, User Experience Questionnaire; WEMWBS, The Warwick-Edinburgh Mental Wellbeing Scale.

Cost-effectiveness by means of the incremental cost-effectiveness ratio (ICER; the difference in mean costs divided by the difference in mean QALYs at the time of recruitment to the study and 1 year before the study and 1 year after the end of the intervention).

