#### Cost-effectiveness analysis (incremental cost-effectiveness ratio)

Total costs for the intervention and control groups will be calculated by summing the following: (1) intervention-specific costs (ie, equipment, technology and software costs); (2) standard care costs (printing and distribution costs of OTAGO HEP and Meniere’s Dizziness booklet, estimated therapist time and healthcare facility usage for standard care participants); and (3) indirect costs of data utilisation of healthcare records 1 year post-intervention to capture primary care services and hospital usage. The *ICER* will be calculated as follows:

$$ICER=\frac{\Delta Cost}{\Delta QALYs}$$

where ΔCost is the difference in average costs between the intervention and control groups, and QALYs is the difference in QALYs gained. To assess the robustness of the ICER, a one-way sensitivity analysis will vary key inputs, such as utility values, cost assumptions and healthcare utilisation rates, to evaluate their impact on the ICER. This will help identify variables with the greatest impact on cost-effectiveness.

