#### Statistical approach for quality-adjusted life year and cost-effectiveness analysis

A mixed-effects regression model will compare QALYs and costs between groups, adjusting for confounders like age, baseline health and site. Cost-effectiveness will be evaluated against willingness-to-pay thresholds (eg, £20 000–£30 000 per QALY in the UK) to determine if TeleRehaB DSS is a cost-effective alternative to standard care.

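### The planned ICER divides costs running to 1 year after the intervention by QALYs that stop at week 10, and is then read against a cost-per-QALY threshold

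*Protocol article*

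**What the plan says.** All places are in the Protocol article.

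- **QALYs (denominator).** Quality-adjusted life years: "Health-related QOL will be assessed using the EQ-5D-5L at baseline and post-intervention", and then "The area under the curve method will estimate QALYs over the intervention period". The Outcome measures section and Table 2 put those two measurements at week 0 and week 10. After week 10 the schedule continues only with monthly falls diaries.
- **Costs (numerator).** Cost-effectiveness analysis sums three components. The third is "indirect costs of data utilisation of healthcare records 1 year post-intervention to capture primary care services and hospital usage". The total feeds the ratio, "where ΔCost is the difference in average costs between the intervention and control groups".
- **Use of the ratio.** Statistical approach for quality-adjusted life year and cost-effectiveness analysis: "Cost-effectiveness will be evaluated against willingness-to-pay thresholds". The UK example is £20 000–£30 000 per QALY, and the stated purpose is to decide whether the system is a cost-effective alternative to standard care.
- **A further time frame.** The sentence on the ICER after Table 2, under Secondary outcome measures, refers to the time of recruitment and to "1 year before the study and 1 year after the end of the intervention". It does not make clear whether this applies to costs, QALYs or both.
- **Sensitivity analysis.** "a one-way sensitivity analysis will vary key inputs, such as utility values, cost assumptions and healthcare utilisation rates". Time horizon and persistence of effect are not among the examples.

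**The concern.** An ICER can be set against a cost-per-QALY threshold only if costs and health effects are counted over the same period. Here the numerator takes in a year of healthcare use after the programme, and the denominator stops when the programme does. No extrapolation of utilities is described that would bridge the gap.

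Two distortions follow. If a benefit lasts beyond week 10, its QALYs are left out while the costs of that period are kept, so with a positive cost difference the ratio comes out too high. If hospital or primary care use falls in the following year, the saving lowers the numerator without the QALYs of that year. The ratio then looks better than a week-10 ratio would, and it would be too favourable if the utility difference had reversed after week 10. Either could put the result on the wrong side of the threshold.

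**Working it through.** The document states no ICER, QALY or cost figure, so there is nothing of its own to reproduce. The check measures the gap between the two horizons.

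**Inputs.** Utility measured at weeks 0 and 10 (Outcome measures, Table 2). Costs to 52 weeks after the intervention (Cost-effectiveness analysis). Threshold £20 000–£30 000. Illustrative week-10 utility differences *d* = 0.03 and 0.52, the ends of the MCID range under Primary outcome measures, and 0.10 as an assumed value between them. Equal baseline utilities are assumed. The persistence patterns after week 10 are also assumptions.

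**Windows.** Costs: 10 + 52 = 62 weeks. QALYs: 10 weeks. Ratio 62/10 = 6.2.

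**QALY difference.**
- To week 10 (trapezoid): 0.5 × *d* × 10/52
- To 1 year after, effect ends at week 10: add 0
- To 1 year after, linear fade to zero: add 0.5 × *d* × 1
- To 1 year after, effect held: add *d* × 1

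**Factor relative to the week-10 figure.** *d* cancels:
- ends at week 10: 1.0
- fades: 1 + 0.5/(0.5 × 10/52) = 1 + 5.2 = 6.2
- held: 1 + 1/(0.5 × 10/52) = 1 + 10.4 = 11.4

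If the area is taken over the 9 programme weeks instead, the last two become 1 + 52/9 = 6.8 and 1 + 104/9 = 12.6.

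**Largest cost difference that passes £20 000–£30 000 per QALY** (threshold × QALY difference):

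| *d* | QALYs to week 10 (also the limit if the effect ends there) | Fade over the year | Held for the year |
|---|---|---|---|
| 0.03 | 0.0029: £58–£87 | 0.0179: £358–£537 | 0.0329: £658–£987 |
| 0.10 | 0.0096: £192–£288 | 0.0596: £1 192–£1 788 | 0.1096: £2 192–£3 288 |
| 0.52 | 0.0500: £1 000–£1 500 | 0.3100: £6 200–£9 300 | 0.5700: £11 400–£17 100 |

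**Effect of later costs.** In the planned ratio, each £1 of cost difference arising after week 10, in either direction, moves the ICER by 1/(week-10 QALY difference). That is £347 per QALY at *d* = 0.03 (1/0.002885), £104 at 0.10 (1/0.009615) and £20 at 0.52 (1/0.05). A week-10 ratio would not contain that £1 at all. In a ratio matched to 1 year with the effect held, it would move the ICER by 11.4 times less.

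**The case against.** The strongest reply is about weight. The ICER is a secondary outcome of a feasibility trial that disclaims power for clinical effectiveness and says it has no formal plan for statistical analysis. No feasibility, safety or usability result depends on it. That stands and limits the consequences. It does not remove the point. The Statistical analysis section says that a plan developed for a future trial is being run here to see whether it is appropriate, and the economic section commits to a threshold reading.

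The sensitivity analysis could be extended, since its inputs are given as examples. But varying inputs one at a time around a mismatched base case does not align the periods. It is also true that only the healthcare-records component is tied to 1 year. It is still summed into the cost difference.

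Three stronger readings are tempting and are not supported:
- *The denominator is 6 to 11 times too small.* This depends wholly on assumed persistence. If the effect ends at week 10, the factor is 1.0.
- *The mismatch turns an ICER of about £15 000 (held) or £28 000 (fading) into £173 000.* Those values follow from *d* = 0.03 and a cost difference of £500, but the £500 is in no document. The same £500 over week-10 QALYs gives £52 000 at *d* = 0.10 and £10 000 at *d* = 0.52. The contrast also shows what a short QALY horizon does, and a matched week-10 analysis keeps that horizon.
- *Secondary outcome measures defines the ICER with QALYs 1 year before and 1 year after.* The sentence is incomplete, and the pre-study year may be meant as a window for healthcare costs. If it does mean QALYs, no scheduled EQ-5D-5L can supply them.

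**Conclusion.** The concern holds as a mismatch of horizons written into the current text: about 62 weeks of costs over about 10 weeks of QALYs, with a threshold decision attached. As planned, the ratio equals a common-horizon 1-year ICER only if the utility difference contributes no net QALYs after week 10, and the document does not assume that.

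The size is conditional. With equal baselines and a 10-week area, the QALY difference over the cost horizon is 1.0, 6.2 or 11.4 times the week-10 figure for an effect that ends, fades linearly or is held. The direction of the error in the threshold conclusion is not fixed, because later costs or savings also enter unmatched. The time frame under Secondary outcome measures is an ambiguity to reconcile, not a proven second definition of the ratio. The problem should be settled before the economic analysis is run. It does not touch the feasibility, safety or usability outcomes.

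**What to change.** Use one horizon for costs and QALYs.

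1. **Base case.** At minimum, compute the ICER with both costs and QALYs from baseline to week 10. Report 1-year healthcare use separately as a cost-consequence result, not divided by 10-week QALYs. State that a 10-week ICER carries the full equipment cost but omits any later benefit, so it is coherent but short-sighted.
2. **If 1-year costs are to stay in a ratio.** Add a labelled scenario analysis that extrapolates utilities to 1 year under no persistence, linear fade and held effect. Present it as dependent on those assumptions.
3. **Reconcile the text.** State in Secondary outcome measures whether the pre-study year is a healthcare-cost baseline, and bring the sentence into line with the two economic sections. Simply deleting it could remove a cost window that was intended.
4. **Optional.** EQ-5D-5L could be collected after week 10 to measure a longer matched horizon. This would need ethics amendments at the sites. The falls-diary contacts are a limited vehicle for it, because they run only for up to 6 months and would not reach the 1-year cost horizon.

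Steps 1 to 3 are changes of wording plus a little more analysis, with no added participant assessment. Cost items must be dated so that they can be cut at week 10. The price is a shorter base-case horizon.

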#### Cost-effectiveness analysis (incremental cost-effectiveness ratio)

Total costs for the intervention and control groups will be calculated by summing the following: (1) intervention-specific costs (ie, equipment, technology and software costs); (2) standard care costs (printing and distribution costs of OTAGO HEP and Meniere’s Dizziness booklet, estimated therapist time and healthcare facility usage for standard care participants); and (3) indirect costs of data utilisation of healthcare records 1 year post-intervention to capture primary care services and hospital usage. The *ICER* will be calculated as follows:

$$ICER=\frac{\Delta Cost}{\Delta QALYs}$$

where ΔCost is the difference in average costs between the intervention and control groups, and QALYs is the difference in QALYs gained. To assess the robustness of the ICER, a one-way sensitivity analysis will vary key inputs, such as utility values, cost assumptions and healthcare utilisation rates, to evaluate their impact on the ICER. This will help identify variables with the greatest impact on cost-effectiveness.

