## Methods

### Trial design

The study is a multicentre, assessor-blinded RCT, investigating the feasibility and acceptability of the TeleRehaB DSS in persons with stroke, MCI, vestibular dysfunction or long covid.^49^ All participants will be enrolled in a 9-week MBR home exercise programme (HEP), including individualised balance exercises (sitting, standing, walking), cognitive training and exergames (figure 1). All participants will be randomised into one of three study arms, where they will receive a HEP provided under the supervision of a clinician (physiotherapist or sports scientist): (1) the high-technology TeleRehaB DSS group (HT-IG), (2) the low-technology TeleRehaB DSS group (LT-IG) or (3) the control group (CG) standard of care HEP. No matter the study arm allocated, all participants will receive the same prescription pattern, receiving a weekly check-in call by a member of the research team, and remote programme reviews at weeks 3 and 6 by the treating clinician, to discuss exercise modifications, symptoms, falls and any technical problems.

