**Figure 4 F4:**
[figure not shown]
Diagram of the TeleRehabilitation Decision Support System (TeleRehaB DSS) high-technology arm (**A**) and low-technology arm (**B**) hardware. In the high-technology arm (**A**), participants use a head-mounted augmented reality (AR) device; four inertial measurement units (IMUs) placed on both ankles, head and trunk; a depth-sensing camera for full-body motion capture; a smartwatch for additional physiological data and an ECG monitor worn on the chest. In the low-technology arm (**B**), participants use a tablet for exercise display, the same four IMUs and ECG monitor, and the depth camera for motion capture.

The TeleRehaB DSS includes an extended version of the HOLOBalance rehabilitation programme delivered via an AR hologram of a virtual physiotherapist. It is based upon established, evidence-based MBR protocols that have been shown to improve balance control in older adults at risk of falls and in persons with vestibular disorders.^23 54 55^ Additional exercises have been added to the TeleRehaB DSS, including range of motion stretching exercises and optokinetic stimulation exercises for participants with visual induced dizziness. Please see online supplemental material table S2 for exercise details and progression levels.

IG participants will be visited by a research team member to instal the TeleRehaB DSS into their home and taught how to use the system, with a practice session. The initial set of exercises will be set by the treating clinician and all subsequent exercise progressions will be suggested by the AI-DSS and either approved or disapproved by the treating clinician. The approved exercise programme will be loaded into the participant’s training plan which will automatically be deployed.

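### The cost sum charges therapist time to standard care only, although TeleRehaB participants also receive clinician reviews, so the cost difference is tilted towards TeleRehaB

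*Protocol article*

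**What the plan says.** The section on cost-effectiveness analysis builds total cost from three items.

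1. Intervention costs: "intervention-specific costs (ie, equipment, technology and software costs".
2. Standard care costs: printing and distribution of the control materials, plus "estimated therapist time and healthcare facility usage for standard care participants".
3. Later healthcare use: "indirect costs of data utilisation of healthcare records 1 year post-intervention to capture primary care services and hospital usage".

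The numerator of the ICER is then fixed: "ΔCost is the difference in average costs between the intervention and control groups". A one-way sensitivity analysis varies utilities, cost assumptions and healthcare utilisation. The next section compares the result with thresholds such as £20 000 to £30 000 per QALY.

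On delivery, the Trial design section puts all three arms under a clinician's supervision and says that "all participants will receive the same prescription pattern, receiving a weekly check-in call by a member of the research team", with "remote programme reviews at weeks 3 and 6 by the treating clinician". The intervention section adds that "IG participants will be visited by a research team member to instal the TeleRehaB DSS into their home", with teaching and a practice session. It also says that the treating clinician sets the first exercises and accepts or rejects each progression that the AI suggests. Table 2 lists equipment removal for the intervention group only.

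**The concern.** Therapist time is named as a cost, but it is tied to one arm. The intervention item holds hardware and software only, and the third item starts after the programme has ended, so it cannot pick up delivery of the 9 weeks. No item holds staff time for TeleRehaB participants, although the same clinicians review them on the same schedule. Facility usage carries the same restriction.

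An input given to both arms should largely cancel in a cost difference. Here it enters as a saving for TeleRehaB. The result is then compared with a willingness-to-pay threshold to decide whether the system is a cost-effective alternative, so the imbalance falls on a stated conclusion. The costing rule would also be carried into the definitive trial that this study is meant to inform.

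**Working it through.** The documents give no cost, QALY difference or ICER, so there is no figure to reproduce. The check has three steps.

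**1. Delivery contacts against the cost list**

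| Contact | TeleRehaB arms | Control | Costed for TeleRehaB? | Costed for control? |
|---|---|---|---|---|
| Clinician reviews, weeks 3 and 6 | yes | yes | no | yes, as therapist time |
| Clinician prescription and progression | yes (first set, then approval of AI suggestions) | yes (clinical judgement with the manual or booklet) | no | yes, as therapist time |
| Weekly research-team call | yes | yes | no | unclear: not necessarily therapist time |
| Home installation, teaching, practice | yes | no | not named | not applicable |
| Equipment removal | yes | no | not named | not applicable |

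**2. Direction**

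Let I be the uncosted staff cost per TeleRehaB participant. Then:

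- planned ΔCost = true ΔCost − I
- net monetary benefit = λ × ΔQALY − ΔCost, which is overstated by I whatever the sign of ΔQALY
- ICER = ΔCost / ΔQALY, which is too low by I / ΔQALY when ΔQALY > 0

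The Discussion expects better quality of life under TeleRehaB, so ΔQALY > 0 is the case that the authors anticipate. If calls are uncosted in both groups and cost the same in each, they drop out, and I covers only reviews, prescription and approvals, set-up and removal.

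**3. Size, for illustration only**

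From the documents: QALYs by area under the curve over the intervention period, assessments at weeks 0 and 10, and an EQ-5D-5L MCID range of 0.03 to 0.52. A linear path gives ΔQALY = 0.5 × gain × 10/52:

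- gain 0.03: 0.5 × 0.03 × 10/52 = 0.00288
- gain 0.52: 0.5 × 0.52 × 10/52 = 0.0500

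Assumed: 3 to 8 omitted staff hours at £30 to £60 per hour, so I runs from 3 × 30 = £90 to 8 × 60 = £480.

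| Utility gain | Shift at £90 | Shift at £480 |
|---|---|---|
| 0.03 | 90 / 0.00288 ≈ £31 000 | 480 / 0.00288 ≈ £166 000 |
| 0.52 | 90 / 0.05 = £1 800 | 480 / 0.05 = £9 600 |

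The role of the calls can be seen in a second assumed set: nine calls of 10 minutes, two reviews of 30 minutes, 2 hours for installation and removal, at £40 per hour. Calls cost 1.5 × 40 = £60, reviews 1 × 40 = £40, and set-up and removal 2 × 40 = £80, in total £180. If calls cancel, £120 remains. That is 120 / 0.00288 ≈ £41 600 per QALY at a gain of 0.03, and 120 / 0.05 = £2 400 at 0.52. Approval time is not in this set, because the article gives no frequency for it.

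At a gain of 0.03, an omission of 20 000 × 0.00288 ≈ £58 to 30 000 × 0.00288 ≈ £87 equals the whole threshold range. At 0.52 the same calculation gives £1 000 to £1 500.

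**The case against.** The best defence is that this is one sentence in a condensed article. Its lead-in speaks of totals for both groups, and the article's use of ie may be loose, so unclear wording is more likely than a decision to cost intervention labour at zero. Installation labour might also be meant to sit under technology costs. That would be persuasive if the article were silent on therapist time. It is not: it names therapist time and limits it to standard care participants, and the lead-in does not undo that limit. Varying cost assumptions changes inputs already in the sum; it does not add a missing category. Even if installation counts as technology, the clinician reviews, prescription and approvals remain outside.

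Several parts of the defence stand. The weekly calls are made by the research team, so they may be uncosted in both groups and cancel. No minutes, wages or equipment prices are given. The large shifts come from the bottom of the MCID range. This is a feasibility study, and the ICER is listed with the secondary outcomes.

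A reader might infer two stronger claims. One is that TeleRehaB participants demonstrably receive at least as much staff time. The contact schedule suggests it, but no durations are given, and AI-drafted progressions could shorten a clinician's task. The other is that the accounting alone would bring the ICER below the threshold. The costed hardware may dominate the cost difference, and without its price no crossing can be shown.

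**Conclusion.** The point holds as a matter of text and direction. Therapist time is costed in one arm and delivered in all, so the planned cost difference is too low by the intervention arms' clinician time, and by set-up and removal labour unless that is counted as technology cost. Net monetary benefit is overstated by that amount, and the ICER is too low if ΔQALY is positive. This is a badly fixed rule, not detail left to another document.

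The size is unknown. The illustrated shift runs from £1 800 to £166 000 per QALY, depending on assumed hours, assumed hourly rates, a linear 10-week area under the curve, and a utility gain anywhere from 0.03 to 0.52. It is smaller if calls cancel. The direction does not depend on these assumptions, provided the omitted staff time has a cost above zero.

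**What to change.** Rewrite the cost sum so that the same categories apply in every arm:

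- clinician and staff time for reviews, prescription and progression, including approval of AI suggestions
- calls, either costed in all arms or left out of all arms
- set-up, training and equipment removal, where they occur
- materials or equipment
- healthcare and facility use

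Estimate or record contact time in all arms, and vary therapist time separately by arm in the one-way sensitivity analysis.

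The cost is a short rewrite and slight extra recording. Randomisation, sample size and clinical outcomes are untouched. The reported ICER will probably be less favourable to TeleRehaB. Contact time is better noted during the trial, because it is hard to recover afterwards.

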#### Control intervention: OTAGO home exercise programme; Meniere’s Dizziness programme

CG participants will receive a standard of care balance rehabilitation HEP; stroke and MCI participants will complete the *OTAGO HEP*^56^,^58^ (accessible at https://www.livestronger.org.nz/assets/Uploads/acc1162-otago-exercise-manual.pdf), while vestibular and long covid participants will complete the *Balance Retraining Booklet*^59 60^ (accessible at https://www.meandve.org.uk/files/pdfs/Balancing_Retraining_(Nov_2023).pdf).

Participants will be required to log their exercises daily on a written diary. The exercises will be reviewed remotely by the treating clinician every 3 weeks. Participants will also be required to complete a falls diary (online supplemental material table S2), which will be reviewed in the weekly telephone call. Exercises will be progressed in line with the recommendations from the OTAGO HEP and/or Meniere’s Dizziness booklet, in combination with the treating clinician’s clinical judgement.

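### The cost definition charges healthcare facility use to control participants only, so any non-zero amount tilts the ICER toward TeleRehaB

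*Protocol article*

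**What the plan says.** The protocol article's section on cost-effectiveness analysis (ICER) opens with "Total costs for the intervention and control groups will be calculated by summing the following", and lists three items:

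- Item (1): "intervention-specific costs (ie, equipment, technology and software costs".
- Item (2), standard care costs: printing and distribution of the two control programmes, plus an estimate of therapist time and "healthcare facility usage for standard care participants".
- Item (3): "indirect costs of data utilisation of healthcare records 1 year post-intervention to capture primary care services and hospital usage". This item is not restricted to one arm.

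On how care is delivered:

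- The control intervention section says: "The exercises will be reviewed remotely by the treating clinician every 3 weeks".
- The trial design section gives every arm the same weekly call and the same remote reviews at weeks 3 and 6.
- The outcome measures section says: "All study participants will attend two sessions at the clinical site: at baseline (week 0) and post-intervention (week 10".
- The intervention section adds a home installation visit with a practice session for the TeleRehaB arms, and Table 2 adds de-installation. Item (1) names neither.

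**The concern.** A cost difference between arms means something only if the same kinds of resource are costed in each arm. Here facility use is named for one arm alone, and that arm follows a home programme with remote supervision. If a positive amount is entered, it comes straight off the incremental cost of TeleRehaB.

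The section on the statistical approach for QALYs and costs will hold the result against £20,000–£30,000 per QALY, and the Discussion offers these data in support of a definitive trial. The QALY section measures benefit over the intervention period only, so the QALY difference in the denominator will be small and the ICER sensitive to modest errors in cost.

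**Working it through.** The article gives no unit cost, QALY difference or ICER, so there is no stated figure to reproduce. The check has two parts.

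**Part 1: what the control-only line could contain**

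| Reading of facility use in item (2) | What the article describes | Effect of charging controls only |
|---|---|---|
| Visits to deliver the control programme | None; home-based, remote review | Nothing to charge |
| Assessment sessions at weeks 0 and 10 | Identical in all arms | Biased; should cancel |
| Facility overhead on clinicians' review time | Reviews at weeks 3 and 6 in all arms | Biased |
| Routine healthcare contacts during the 9 weeks | Can occur in any arm; outside item (3) as dated | Biased |
| Contacts after the programme | Collected by item (3) in both groups | Biased, and counted twice for controls |

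No reading supports a positive charge to controls alone. Overlap with item (3) arises only under the last one, or if the records also reach back into the programme.

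**Part 2: how much a control-only charge moves the ICER**

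Inputs from the article:

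- ICER = ΔCost / ΔQALY (cost-effectiveness section).
- QALYs by area under the curve over the intervention period, with EQ-5D-5L at baseline and post-intervention (QALY section); post-intervention is week 10 (Table 2).
- EQ-5D-5L MCID range 0.03 to 0.52 (primary outcome section), used only to span possible utility differences *u*.
- Thresholds £20,000 and £30,000 per QALY.

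Assumptions not in the article: equal baseline utility, linear change to a difference *u* at week 10, an intermediate *u* of 0.10, and a charge *F* of £100 per control participant.

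Formulas:

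- ΔQALY = 0.5 × *u* × 10/52
- ΔCost as calculated = true ΔCost − *F*
- Fall in ICER = *F* / ΔQALY, for ΔQALY > 0
- Value of the gain = threshold × ΔQALY

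| *u* | ΔQALY | Fall in ICER per £100 | Value at £20,000 | Value at £30,000 |
|---|---|---|---|---|
| 0.03 | 0.5 × 0.03 × 10/52 = 0.0029 | about £34,700 | £58 | £87 |
| 0.10 | 0.5 × 0.10 × 10/52 = 0.0096 | £10,400 | £192 | £288 |
| 0.52 | 0.5 × 0.52 × 10/52 = 0.050 | £2,000 | £1,000 | £1,500 |

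With 9 weeks in place of 10, the falls per £100 are about £38,500, £11,600 and £2,200.

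**The case against.** A reader might infer from items (2) and (3) together that control costs are counted twice. The article does not say so. The cost section dates item (3) to the year after the intervention. The ICER definition beneath Table 2 refers to a year before the study and a year after the end of the intervention. Neither names the 9 weeks. Item (2) sits beside printing and therapist time and has no window, so it reads naturally as delivery during the programme; on that reading nothing is counted twice. This stands: a double count is a possibility left open, not a stated rule. The tilt does not need it, because one-sided charging is enough.

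The line may also turn out to be empty. If zero is entered there is no bias, so the finding is conditional on a positive amount. The pound figures depend on *u* as well: near the top of the quoted range, £100 matters little.

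Therapist time is arguably the clearer half of the same asymmetry. It too is tied to standard care, although clinicians set, approve and review exercises in the TeleRehaB arms. That widens the remedy but does not excuse the facility line.

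Finally, this is a feasibility study reported in an article, and costing detail may sit elsewhere. But the article states the cost rule itself and commits to a threshold comparison. The planned one-way sensitivity analysis varies the size of inputs, not which arm bears a category. Adjusting the regression for age, baseline health and site does not correct a cost assigned by arm.

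**Conclusion.** The point holds as an asymmetry in the stated cost definition. Facility use is listed for control participants only, without support in the described design, and each pound charged this way understates ΔCost by one pound in TeleRehaB's favour. The direction of the cost error does not depend on the QALY result; the fall in the ICER shown above assumes a positive ΔQALY.

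The size cannot be fixed from the document. As an illustration, a charge of £58–£87 per control participant equals the whole threshold value of a 0.03 utility gain by week 10, so it could change the conclusion at small effects. At 0.52 the corresponding sum is £1,000–£1,500. Overlap with item (3) should be ruled out by wording, but should not be reported as an established double count.

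**What to change.** Reword the cost definition as follows:

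1. Remove the control-only facility charge from item (2).
2. Apply the same delivery-cost categories to all arms: clinician time, calls and reviews, home visits including installation and de-installation, and any facility use.
3. Count primary-care, outpatient and hospital use once, from records, with the same unit costs in all arms, over one stated window that includes the 9-week programme. Deleting the phrase while leaving item (3) dated as it is would leave use during the programme uncosted in every arm.
4. Exclude the two research assessment visits from all arms.

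This is mainly a change of wording. The downside is slightly more records extraction to cover the programme period.
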